## Discussion

Given that AD is a common pediatric skin disease with an increasing economic burden and limitations of clinical medication, there is an urgent need to develop new strategies for disease prevention in infants. Studies on the gut–skin axis have revealed the key role of gut microbiome dysbiosis in the development of immune-mediated AD (Mahmud et al., 2022). Supplementing mothers with probiotics during late pregnancy and lactation is effective in preventing AD in their offspring, whereas supplementing infants alone with probiotics may not be effective in alleviating AD (Baldassarre et al., 2018). Probiotic supplementation during pregnancy increases the IFN-γ level in cord blood and immunomodulatory factors in breast milk (Prescott et al., 2008). Infants may develop AD when they have impaired IFN-γ activation, which disrupts the Th1/Th2 balance and leads to AD (Herberth et al., 2010; Brar and Leung, 2016). Studies have also revealed that human breast milk is a source of commensal bacteria that are beneficial for the gut health of offspring (Lyons et al., 2020). Gut-specific strict anaerobes and facultative anaerobic bacteria such as *Bifidobacteria* and *Lactobacilli* can be detected in breast milk (Gronlund et al., 2007). Two IgA molecules in the intestinal tract bind to each other through secreted fragments to form sIgA, which can wrap around bacteria in the intestinal tract (Rochereau et al., 2013). sIgA-coated bacteria can be transported into intestinal Peyer’s patches and carried by dendritic cells to the mammary glands (Macpherson and Uhr, 2004).

The mechanism of probiotic transmission from mothers to infants remains unclear, which hinders the isolation, screening, and application of probiotic strains for AD prevention. We previously observed that sIgA-coated bacteria are key functional bacteria for vertical transmission between mother and child and that breast milk is a good source of sIgA-coated probiotics (Cui et al., 2020; Ding M. et al., 2022). *Limosilactobacillus reuteri* is a well-studied probiotic bacterium detected in breast milk (Mu et al., 2018). Previous studies have reported the therapeutic potential of *L. reuteri* in the management of allergic diseases (Forsythe et al., 2007; Karimi et al., 2009). Using a patented technology developed by our group, sIgA-coated *L. reuteri* FN041 was isolated. Preclinical experiments have confirmed the therapeutic potential of *L. reuteri* FN041 in preventing AD (Qi et al., 2021; Zhou et al., 2022). Maternal mice supplemented with *L. reuteri* FN041 can promote the expression of intestinal antimicrobial peptides and enhance the mucosal barrier function and intestinal sIgA production by remodeling the gut microbiota in their offspring (Qi et al., 2021).

A previous study showed that no adverse reactions were observed in individuals supplemented with live *L. reuteri* at a daily dose of 1 × 10^8^ to 1 × 10^10^ CFU (Mobini et al., 2017). A meta-analysis of eight randomized controlled trials of probiotic application in >1,500 pregnant females also revealed that probiotic consumption from 32 to 36 weeks of gestation did not increase the incidence of abortion or malformations and had no effect on birth weight, gestational age, or delivery mode (Dugoua et al., 2009). In the first stage of this clinical trial, we will assess the safety of maternal *L. reuteri* FN041 supplementation. We aim to determine the optimal dose of maternal *L. reuteri* FN041 during pregnancy and lactation for infantile AD prevention. In the second stage of the study, we intend to promote the application of maternal *L. reuteri* FN041 supplementation in a multicenter setting to evaluate the incidence of AD after the intervention. In addition, *L. reuteri* FN041 in breast milk and infant feces, detected using metagenomic sequencing and StrainPhlAn3 analysis, indicate that a specific strain *L. reuteri* FN041 can be transmitted to infants through breast milk, providing new evidence for vertical transmission in maternal and infant microbiomes.

Importantly, previous clinical studies have confirmed the protective action of a mixture of probiotics against AD. Here, we aim to identify the potential role of a more efficient single strain of *L. reuteri* FN041 in AD prevention. We have discovered that its ability to adhere to mucus is far superior to that of LGG and *L. reuteri* DSM17938 (unpublished data), which may explain its better preventive effect against AD than LGG and *L. reuteri* DSM17938 in an established AD mouse model (Zhou et al., 2022).

In addition, the regulations regarding the consumption of probiotics by infants in China are strict. Currently, only 14 strains of probiotics are allowed for infants under 1 year of age, and the approval of these 14 strains for infant consumption is mainly based on safety considerations rather than functional perspectives. Notably, all commercial strains used to prevent AD in clinical practice are isolated from the intestines of Western adults, and China has not yet developed probiotics for preventing AD. Therefore, there is an urgent need to identify probiotics in domestic breast milk that can effectively prevent infantile AD. The results of this clinical trial provide evidence for the efficacy of *L. reuteri* strain FN041 isolated from breast milk in preventing or curing AD in infants and provide practical advice for the supplementation of specific probiotics for the primary prevention of AD in pregnant females. Because the immunological mechanisms of AD are similar to those of other allergic diseases, understanding the mechanisms of breast milk-derived probiotic strains can contribute to their application in maternal nutritional intervention strategies to prevent diseases caused by the interaction between the infant intestinal microbiota and the immune system.

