### Objectives

This study aims to assess the incidence of infantile AD after maternal consumption of *L. reuteri* FN041 during late pregnancy and lactation. The optimum dosage will be determined by analyzing the efficacy of maternal supplementation with different doses of *L. reuteri* FN041 in preventing AD in offspring. Additionally, the secondary objective is to identify the transfer efficiency of *L. reuteri* FN041 from the mother’s gut to breast milk and then to infant’s gut after oral supplementation.

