### Interventions

#### Intervention strategy

The *L. reuteri* strain used in this study is a probiotic supplement derived from breast milk and formulated in the form of a solid beverage with highly acceptable properties. The solid beverage contained fructooligosaccharides, erythritol, stachyose, resistant dextrin, strawberry juice powder, and vitamin C. The products of the solid beverages with and without *L. reuteri* have the same taste and are packed at 1.5 g per package. *Limosilactobacillus reuteri* has been reported to colonize the intestines of almost all vertebrates and mammals, has good biocompatibility, and is widely used for food production. We previously used targeted sIgA immunomagnetic bead enrichment and separation technology (patent number ZL201610975479. X) to isolate a strain of sIgA-coated *L. reuteri* FN041 (patent strain storage number: GDMCC60546) from Gannan breast milk. This species is included in the list of bacterium strains that can be used for food released by the National Health Commission and is a probiotic that can be used in ordinary food. Genome sequencing analysis revealed that *L. reuteri* FN041 has no horizontally transmissible antibiotic resistance or pathogenic genes.

The selected doses (1 × 10^9^, 5 × 10^9^, and 1 × 10^10^ CFU/d) of *L. reuteri* FN041 in the first stage are in the reported safe range and the optimal dosage will be determined and subsequently applied in the second stage. The World Allergy Organization recommends probiotic administration to pregnant females at high risk of bearing a child with allergy during pregnancy and, in case of breastfeeding, lactation (Fiocchi et al., 2015). Therefore, oral intervention with the respective solid drinks for the recruited subjects in the two stages will start from the gestational age of 32–36 weeks until delivery. The mothers will continue to consume the corresponding solid drinks daily for 6 months, from 1 to 3 days after delivery, during the lactation period. All the solid drinks are suggested to be taken orally at bedtime once daily.

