### Data collection and sample collection

Clinical follow-up of the infants will be conducted at 7 and 42 days of age, and telephone follow-up will be conducted at 6, 12, and 24 months of age. Questionnaire surveys will be completed at each clinical and telephone follow-up. The infant-specific questionnaire is designed based on the International Study on Asthma and Allergy in Children. Detailed information on birth parity, number of births (single or multiple births), gestational age, mode of delivery, weight (including birth weight), length (including birth length), feeding mode (breast, formula-, or mixed-fed), maternal and infant exposure to antibiotics and probiotics, parental smoking, family history of allergic diseases, infection, and other potential confounding factors will be recorded.

The mother’s feces will be collected within 1 week before intervention with solid beverage and the first week after delivery, whereas breast milk samples (approximately 5–10 mL each time) will be collected at 1–6 (colostrum), 7–15 (transitional milk), and 16–30 (mature milk) d after childbirth. Cord blood will be collected at the time of birth. Fecal samples (approximately 0.5–6 g each time) will be collected from infants in the colostrum, during transitional lactation, and at the ages of 1, 6, and 12 months after birth.

The maternal dietary survey is designed to be carried out before and after probiotic intervention (that is, 6 months after delivery). The dietary and nutritional status survey will be conducted using a 24-h dietary recall method to investigate the intake of various foods by the study participants within 3 days. Their energy and nutrient intake will be analyzed. The food frequency questionnaire will be used to collect information on the types and frequencies of food intake among all study participants and evaluate their dietary structure.

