#### Secondary outcomes

The severity of gastrointestinal and respiratory symptoms will be analyzed as a secondary outcome. Meanwhile, regulatory T cells in umbilical cord blood at birth (*n* = 20 for each group) will be analyzed via flow cytometry and the levels of transforming growth factor-β, interleukin (IL)-10, IL-12, IL-13, IL-4, interferon-γ (IFN-γ), tumor necrosis factor-α, and total IgE will be determined using enzyme-linked immunosorbent assay. Further, colostrum and 42-day mature milk level of transforming growth factor-β and IL-10 will be tested. Moreover, the relative abundance of sIgA-coated *L. reuteri* FN041 will be analyzed in breast milk and infant feces using strain-specific PCR, depending on the genome sequence information. *Lactobacillus* strains will be isolated and determined using 16 s rRNA sequencing, metagenomic sequencing will be performed to analyze *L. reuteri* FN041 (*n* = 10 for each group), and StrainPhlAn3 will be used to analyze the data at the strain level (Walsh et al., 2017).

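### Finding FN041 in both breast milk and infant stool supports mother-to-infant transfer, but not the milk route or its direction, which the Discussion says it will show

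*Protocol article*

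**What the plan says.** The Objectives section sets the secondary aim as the efficiency of transfer "from the mother’s gut to breast milk and then to infant’s gut after oral supplementation". The abstract gives the same chain as the secondary outcome.

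Under Secondary outcomes, sIgA-coated FN041 "will be analyzed in breast milk and infant feces using strain-specific PCR, depending on the genome sequence information"; metagenomic sequencing with strain-level analysis is planned for 10 per group. The Discussion then states how these data will be read: FN041 "in breast milk and infant feces, detected using metagenomic sequencing and StrainPhlAn3 analysis, indicate that a specific strain" of *L. reuteri* "can be transmitted to infants through breast milk, providing new evidence for vertical transmission in maternal and infant microbiomes".

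On exposure, the Intervention strategy section says that the drinks "will start from the gestational age of 32–36 weeks until delivery", and that mothers then continue daily "for 6 months, from 1 to 3 days after delivery, during the lactation period".

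On sampling, the Data collection section lists milk at days 1–6, 7–15 and 16–30 after birth. Infant stool is listed in the colostrum and transitional periods and at 1, 6 and 12 months. Maternal stool is listed within the week before dosing and in the first week after delivery. The recorded covariates include "mode of delivery, weight (including birth weight), length (including birth length), feeding mode (breast, formula-, or mixed-fed").

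**The concern.** The objective concerns a route, whereas the stated evidence is presence in two places. A mother dosed from late pregnancy may carry FN041 in her gut at delivery and takes a live product every day afterwards. Her infant could acquire the strain at birth or by contact, and the infant's mouth could carry it into the milk. Each of these can leave FN041 in both milk and stool, just as milk transfer would.

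This matters because the Background rests the case for maternal dosing on milk transfer. It attributes the failure of another strain given to mothers to poor passage through milk, and calls passage from the mother's gut to milk the key to prevention. If co-detection is read as the Discussion proposes, the trial could report its central mechanism as shown from data that fit other routes equally well.

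**Working it through.** The plan gives no figure to reproduce here. The check has four parts.

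**1. Does the milk-by-stool table identify direction?** All rates below are assumed; the document gives none.

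*Milk-to-infant model.* P(milk+) = 0.60, P(stool+ | milk+) = 0.70, P(stool+ | milk−) = 0.10.

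*Infant-to-milk model* (infant colonised first by birth or contact, milk seeded afterwards). P(stool+) = 0.42 + 0.04 = 0.46, P(milk+ | stool+) = 0.42 / 0.46 = 0.913, P(milk+ | stool−) = 0.18 / 0.54 = 0.333.

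| Cell | Milk-to-infant | Infant-to-milk |
|---|---|---|
| milk+, stool+ | 0.60 × 0.70 = 0.42 | 0.46 × 0.913 = 0.42 |
| milk+, stool− | 0.60 × 0.30 = 0.18 | 0.54 × 0.333 = 0.18 |
| milk−, stool+ | 0.40 × 0.10 = 0.04 | 0.46 × 0.087 = 0.04 |
| milk−, stool− | 0.40 × 0.90 = 0.36 | 0.54 × 0.667 = 0.36 |

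The tables agree, and not because of the rates chosen. Any joint distribution factors both ways, P(milk) × P(stool | milk) = P(stool) × P(milk | stool), so every milk-first table has an infant-first twin. A larger sample estimates the same four cells more precisely and still does not choose between the models. Strain typing makes each positive more certain to be FN041, but does not show how it arrived.

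**2. Does the placebo arm separate the routes?** Suppose FN041 is absent under placebo (again assumed). The excess of jointly positive pairs is then 0.42 − 0 = 0.42 under either model. Milk, birth and contact transfer all follow from supplementing the mother, so randomisation attributes FN041 in the infant to supplementation but does not divide it by route.

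**3. Does sample timing settle order?** The first milk window (days 1–6) is also the colostrum period in which the first infant stool is taken, and the transitional samples coincide in the same way. No stool before first feeding is listed. Two positives first seen in the same window leave the order open. Only milk positive in a strictly earlier window than the first positive stool is informative, and even that does not exclude contact. The listed milk schedule ends at day 30 (a 42-day milk sample is named only for cytokines), so the 6- and 12-month stools have no listed concurrent milk sample.

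**4. How precise is the sequencing subset?** Exact (Clopper-Pearson) 95% intervals for 10 per group:

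| Positive | 95% interval |
|---|---|
| 0 of 10 | 0% to 30.8% |
| 5 of 10 | 18.7% to 81.3% |
| 7 of 10 | 34.8% to 93.3% |

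These apply to metagenomic sequencing only; no such limit is stated for strain-specific PCR. The low precision is secondary to the identification problem in steps 1 to 3.

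**The case against.** The strongest reply is that the sentence sits in the Discussion and speaks of what the strain *can* do. Neither Statistical methods nor Secondary outcomes contains a rule that classifies a mother-infant pair as milk transmission when both samples are positive, and an article may leave the route analysis to a fuller document. A reader might infer such a per-pair rule, but the text does not state one. What remains is that this sentence is the only place where the article says how the milk and stool results will be read, and that reading names the milk route.

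A second reply is that the design holds more than bare co-detection. The assay targets sIgA-coated FN041, and the Background and Discussion link sIgA coating to passage from gut to breast. There is a randomised placebo arm, maternal stool before and after dosing starts, serial samples, and delivery and feeding mode listed among potential confounders. All of this counts. The sIgA measurement is suggestive of the milk route, but coating does not show by which path the infant acquired the strain. The covariates and serial samples can probe the route, although the article does not connect them to it.

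Three stronger readings are tempting and should be resisted:

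- *The secondary objective goes unanswered.* The placebo contrast can answer whether supplementation of the mother brings FN041 to the infant; only the attribution to milk is unsupported.
- *Mothers are colonised from 32–36 weeks.* The document says only that dosing starts then.
- *The share of falsely attributed pairs can be calculated.* Assuming, say, 40% acquisition by other routes and 50% milk positivity gives 0.40 × 0.50 = 20%. Neither rate is in the document, and the product presumes independence, which infant-to-milk seeding would break.

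**Conclusion.** The concern holds in limited form. Detection of FN041 in both milk and infant stool, even at strain level and even if more frequent than under placebo, supports mother-to-infant transfer. It does not establish milk as the route, or milk-to-infant as the direction. The identification result is algebraic and does not depend on the assumed rates. It does assume that birth, contact or infant-to-milk transfer is possible, which dosing before and after delivery and overlapping sampling leave open.

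The document gives no basis for saying how much transfer would be misattributed. The consequence is an over-claim on a named secondary objective and on the mechanism behind maternal dosing. The primary outcome and the choice of dose on efficacy against atopic dermatitis do not depend on it.

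**What to change.** - In the abstract, Objectives and Discussion, limit the confirmatory conclusion to *FN041 transfer from supplemented mother to infant versus placebo, route not established*. The placebo contrast exists in the first stage only.
- Draw the 10 per group for sequencing from mother-infant pairs with dated milk and stool samples.
- Include the maternal stool already collected in the FN041 assay, so that the first link of the chain is measured.
- Report as exploratory evidence on route (a) the order of first detection, counting milk as first only when it is positive in a strictly earlier window than the first positive stool, and (b) stool detection by recorded feeding mode and delivery mode.
- State the limits of (b). Feeding mode is not randomised and goes with maternal contact, and because breastfeeding is encouraged the group receiving no mother's milk may be small. Neither (a) nor (b) should be made a test that establishes the route.

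The cost is a weaker mechanistic claim, a selection rule for the sequencing subset, and a few extra assays on samples already planned. No added participants or visits are needed.

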### Trial status

This study is in its first stage, from October 2022 to December 2025. Subject recruitment in the first stage commenced from July 2023 and will be continued till December 2023. Subject recruitment in the second stage will start from July 2024 to December 2024.

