**Methods:**

First, a randomized, double-blind, placebo-controlled intervention study will be conducted on 340 pregnant females with babies at high risk for AD. These subjects will be randomly divided into four groups of different doses of *L. reuteri* FN041 (1 × 10^9^, 5 × 10^9^, and 1 × 10^10^ CFU/d) along with a placebo. The safety and efficacy of maternal use of *L. reuteri* FN041 for preventing infantile AD will be analyzed, and the most efficient dosage of *L. reuteri* FN041 will be determined. Subsequently, a multicenter cohort study of 500 pregnant females with babies at high risk for AD will be conducted to promote the maternal application of *L. reuteri* FN041. These subjects will be administered *L. reuteri* FN041 at the optimal dose determined during the first stage of late pregnancy and lactation, and their babies will be analyzed for AD development. Recruitment was initiated in October 2022.

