### Trial design

The study is divided into two stages. In the first stage, a multicenter, randomized, double-blind, placebo-controlled intervention study will be conducted in 340 pregnant females with babies at high risk for AD recruited from the Wuxi Maternity and Child Health Care Hospital affiliated with Jiangnan University and the Affiliated Hospital of Qingdao University. These subjects will be randomly divided into four groups (*n* = 85 for each group): (1) placebo group administered with the carrier solid beverage daily, (2) group administered with *L. reuteri* FN041 solid beverage at a dose of 1 × 10^9^ CFU/d, (3) group administered with *L. reuteri* FN041 solid beverage at a dose of 5 × 10^9^ CFU/d, and (4) group administered with *L. reuteri* FN041 solid beverage at a dose of 1 × 10^10^ CFU/d. Their offspring will be examined for AD development during the 2 years after birth so that the efficacy of maternal use of *L. reuteri* FN041 in the prevention of AD can be analyzed by calculating the cumulative incidence of AD in infants. Adverse reactions will be also recorded. Studies have reported that the most efficient dosage of *L. reuteri* FN041 can be determined within 6 months after birth, as infantile AD often develops in early life and peaks in the third month of life (Guo et al., 2019).

In the second stage of *L. reuteri* FN041 promotion and application, a multicenter cohort study in an expanded research population will be conducted. A total of 500 pregnant females with babies at a high risk for AD will be recruited from four tertiary hospitals: Wuxi Maternity and Child Health Care Hospital affiliated with Jiangnan University, Affiliated Hospital of Qingdao University, Suzhou Municipal Hospital, and Changzhou Maternal and Child Health Hospital. These subjects will be administered with *L. reuteri* FN041 at the optimal dosage determined in the first stage during late pregnancy and lactation; subsequently, their babies will be followed up for AD development for 2 years after birth.

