#### Allocation and blinding

The participants recruited in this study will be grouped randomly in the first stage of project implementation so that they are consistent with each group according to their age, economic situation, educational level, and other influencing factors.

In the first stage, both the on-site and laboratory analyses will be conducted using a double-blind method. The samples of *L. reuteri* and placebo used in the experiment will be processed and produced by a third-party company. The project organizer, researchers, and participants will not be informed about the intervention methods they receive. The biological samples analyzed by laboratory technicians (including blood, breast milk, and feces) will be blinded to their specific sources and grouping situations until the end of all experiments.

In the second stage, a multicenter cohort study will be conducted, in which the recruited subjects will not be blinded because this stage has been designed to explore the efficacy of maternal intervention with *L. reuteri* in preventing infantile AD.

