### Participant timeline

Pregnant females will be recruited at 14–16 weeks of gestation and receive intervention strategy at 32–36 weeks of gestation. Their infants will be followed-up for 2 years after birth. Clinical follow-up will be conducted in the hospital at 1, 3, 6, 8, and 12 months of age, and telephone follow-up will be conducted at 2, 4, 5, 10, and 24 months of age. Two specific pediatric attending doctors are responsible for the clinical follow-up of the infants. Infants suspected of having AD will be referred to the pediatric dermatology clinic, and two designated pediatric dermatologists will jointly diagnose and assess disease severity. Questionnaire surveys will be completed at each clinical and telephone follow-up. Parents will be instructed to contact the project team immediately and take the infant to two designated pediatric dermatologists for diagnosis and treatment if the baby is suspected of developing AD during 0–2 years of age. A detailed flowchart of the study is shown in Figure 1.

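### Stage 1 is dated to end in December 2025, but on the stated recruitment dates its last infants reach the 24-month primary outcome only between late May and the end of June 2026

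*Protocol article*

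**What the plan says.** **Stage dates (Trial status).** "This study is in its first stage, from October 2022 to December 2025". On accrual: "Subject recruitment in the first stage commenced from July 2023 and will be continued till December 2023". On the next stage: "Subject recruitment in the second stage will start from July 2024 to December 2024".

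**Recruitment start (abstract, Methods).** "Recruitment was initiated in October 2022". In Trial status, October 2022 is the start of the stage, and recruitment starts nine months later.

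**Gestational timing (Participant timeline).** "Pregnant females will be recruited at 14–16 weeks of gestation and receive intervention strategy at 32–36 weeks of gestation". Infants are then followed for 2 years.

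**Primary outcome (Primary outcomes).** Cumulative incidence of AD within 2 years of delivery, in both stages.

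**Contacts after 12 months.** The Participant timeline and the Data collection section list different visit schedules. Both have a telephone call at 24 months as the only scheduled contact after 12 months.

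**Dose decision (Trial design).** The most efficient dosage "can be determined within 6 months after birth, as infantile AD often develops in early life and peaks in the third month of life". Stage 2 then uses that dosage.

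**Blinding in stage 1 (Allocation and blinding).** "The project organizer, researchers, and participants will not be informed about the intervention methods they receive". No date is given at which this ends for those roles.

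**The concern.** A woman enrolled in December 2023 at 14–16 weeks delivers around late May or June 2024, and her infant is 2 years old in mid-2026. A stage that ends in December 2025 ends before its own primary outcome has been observed in those infants. If anyone worked to the stated end date, the 24-month result would be either incomplete or measured at a shorter and uneven follow-up.

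The calendar also raises a question about the link between the stages. Stage 2 depends on a dose chosen from 6-month data in stage 1, and the stated dates leave little or no room between the two. The choice needs a comparison by arm while stage 1 still has about 18 months of double-blind follow-up to run. From then on, detection of AD relies on one telephone call and on parents bringing a suspected case to the designated dermatologists, so arm-level results reaching families or follow-up staff could influence it.

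**Working it through.** **Inputs from the article.** Stage-1 recruitment 1 July to 31 December 2023 (184 days); alternative start 1 October 2022 (457 days to 31 December 2023); enrolment at 14–16 weeks; product start at 32–36 weeks; primary outcome at 24 months; 340 women; stage-2 recruitment from 1 July 2024.

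**Assumptions not in the article.** Births at 37–40 weeks, uniform accrual, and 31 December 2025 as the end date, which is the most generous reading.

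**Step 1: last 24-month date.** Birth = enrolment + (gestational age at birth − gestational age at enrolment).
- Shortest lag: 37 − 16 = 21 weeks = 147 days. 31 December 2023 + 147 days = 26 May 2024; 24 months on 26 May 2026.
- Longest lag: 40 − 14 = 26 weeks = 182 days. 31 December 2023 + 182 days = 30 June 2024; 24 months on 30 June 2026.

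The article's December 2025 is not reproduced under any of these. For every infant to be 24 months old by 31 December 2025, the last birth had to be by 31 December 2023. The last enrolment would then have been between 2 July and 6 August 2023.

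**Step 2: share short of 24 months on 31 December 2025.** Recruitment closes exactly 24 months before that date, so the women whose infants fall short are those enrolled in the last *lag* days of the window. Share short = lag ÷ window length.

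| Lag | July 2023 start (184 days) | October 2022 start (457 days) |
|---|---|---|
| 147 days (16 wk, born 37) | 147/184 = 79.9% | 147/457 = 32.2% |
| 175 days (15 wk, born 40) | 175/184 = 95.1% | 175/457 = 38.3% |
| 182 days (14 wk, born 40) | 182/184 = 98.9% | 182/457 = 39.8% |

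The middle row with the July start is about 323 of 340 infants. Births at 41 weeks to women enrolled at 14 weeks (189 days) take the two columns to 100% and 41.4%.

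**Step 3: how much follow-up is missing.** The youngest infant, born 26 May to 30 June 2024, is 18 to 19 months old on 31 December 2025. All visits scheduled up to 12 months are done and the 24-month call is outstanding.

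**Step 4: stage 2 against the 6-month data.**
- Earliest stage-2 product start: 1 July 2024 + (32 − 16) weeks = 21 October 2024.
- Latest start for a woman enrolled that same day: 1 July 2024 + (36 − 14) weeks = 2 December 2024.
- Last stage-1 infant at 6 months: 26 November to 30 December 2024.
- Largest gap: 21 October to 30 December = 70 days = 10 weeks. With a 2 December start and a last 6-month date of 26 November, there is no gap.
- Share of stage-1 infants aged 6 months on 21 October 2024: 62–81% (July 2023 start) or 85–92% (October 2022 start).

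**The case against.** The strongest reply is that Trial status is a short administrative note. It fixes no data lock or analysis date and does not say that follow-up is cut. The rest of the article consistently gives 2 years of follow-up and a 2-year outcome, so a wrong date is likelier than a plan to truncate. This stands. A reader might infer that the primary outcome will be reported on a small minority of infants; the article does not say so. That would follow only if the December 2025 date overrode the 2-year outcome.

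Second, the share short of 24 months counts infants and does not measure information lost. All are about 18 months or older, and the Sample size section quotes cumulative incidences of about 40.1% at 1 year and 41% at 2 years, which suggests few late events. This stands in part. The pair is drawn from earlier studies abroad and is not one cohort's curve. Cases arising after 12 months would also be known only if parents came forward, because the remaining scheduled contact is the one that would be lost.

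Third, the dose-timing gap is marginal. The article says the dose can be determined within 6 months and points to a peak in the third month; it does not require every infant to complete 6 months. This stands, and it makes the point secondary.

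Fourth, a reader might infer that the dose will be chosen by the staff who run follow-up, and so that the blind will be broken. The article does not say who makes the comparison, and a full protocol may provide for a separate analyst. No breach is shown.

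**Conclusion.** The stage-1 end date is wrong as written. With recruitment to the end of December 2023 and births at 37–40 weeks, the 24-month outcome cannot be complete before a date between 26 May and 30 June 2026, five to six months after the stated end. This does not depend on which recruitment start is correct or on the accrual pattern.

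The share affected does depend on them: about 80–99% with the July 2023 start and 32–40% with October 2022, both under uniform accrual. In either case what is missing is the last five to six months at most and the 24-month call. The two recruitment starts contradict each other and need correcting in their own right.

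The stage-2 timing is a lesser point: a gap of up to about 10 weeks for the earliest women, which closes under some allowed timings. The overlap between dose choice and blinded follow-up is a fact of the calendar, and the safeguard for it is something to confirm.

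**What to change.** 1. Restate stage-1 completion as the last infant's 24-month contact, about mid-2026 plus a visit window, and state that the primary analysis is held until then.
2. Give one recruitment start date in both the abstract and Trial status. If October 2022 is when the stage began and not when the first woman was recruited, say so.
3. Reconcile the stage-2 start with the 6-month dose decision. Either state that the decision may use incomplete 6-month data, or move recruitment. A 10-week move would open it on about 9 September 2024 (9 September + 16 weeks = 30 December 2024). With the six-month recruitment length kept, the last stage-2 24-month contact moves from about 1 July 2027 to about 9 September 2027.
4. Confirm that the 6-month comparison by arm is run by someone outside follow-up, and that only the chosen dose is released until the last stage-1 24-month contact. Name who holds the allocation code; the article says only that a third party makes the products.

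Items 1 and 2 cost corrected dates and a later stage-1 report. Item 3 costs a sentence or about 10 weeks. Item 4 costs an access rule. None needs more participants.
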